### Interventions

#### All villages

The eligible inhabitants of all villages will receive an explanation of nidotherapy and a rounded assessment of their present circumstances, their personal strengths and motivations and mental health status. This is presented as a cursory mental health assessment but with no further intervention. A good assessment of general functioning and personality is an important part of environmental selection in nidotherapy.

#### Nidotherapy villages

The procedure described for all villages will be followed, but in the active nidotherapy villages further assessments before any changes will include an environmental analysis involving social, physical and personal aspects, matching of personality characteristics with the development of an environmental intervention using a formal procedure (or if no intervention is required, a plan for future change) and a timetable (nidopathway) with subsequent monitoring of progress.^
24
^ As the choice of environmental change is made by the patient, the intervention course cannot be predicted in advance; however, in most cases we expect that the main components will be completed within 2 months, and for the purposes of the trial all facilitated interventions will be completed by 3 months.

Nidotherapy will be administered by trained environmental facilitators under the supervision of [name], who has completed training in the subject by a combination of theoretical learning and practice under supervision. This enables a full assessment of personality strengths and motivations and allows the right choice of intervention to follow. Some of the practical aspects of achieving environmental change may also require nidotherapy volunteers who have also been trained in the principles of nidotherapy. Each nidotherapy intervention will be classified by a central team as an individual intervention (one designed for that person or family alone) or a community intervention (defined as one that requires the support and involvement of at least 10 members of the village). In some cases, both individual and community interventions may satisfy these definitions.

Examples of the changes achieved in nidotherapy range from community ones to improve social isolation to employment interventions, improving local amenities, help in relationships and bigger changes such as a change of housing arrangements. The main advantage of community involvement is joint decision-making between members of the village, allowing shared benefits to be attained. If nidotherapy is embraced across the village, further benefits could be achieved. In many studies of desired interventions, equipoise is not present. In this study, because we have no previous data, equipoise is achieved, as it is quite possible that residents in the villages may be discomfited by assessments of their mental health and satisfaction, and view any attempts at intervention as interference in the smooth life of the village. The population being studied is not a typical one and is unlikely to be representative of the population with respect to mental health, even though suicide rates are higher in rural than urban areas. However, it has the advantage of being a relatively stable population whose circumstances are normally unchanging in the short term.

### Qualitative project

We plan to conduct qualitative work towards the end of the trial to achieve the following.Assess the acceptability and feasibility outcomes of nidotherapy.Identify the factors associated with changes in outcome reporting.

A random non-stratified sample of trial completers will be approached, and those who consent will undergo semi-structured individual interviews, mainly in-person or via teleconferencing, during or after the final follow-up period. An interview guide will be developed and will likely contain prompts on the following:participants’ initial expectations of the trial;their experience of the assessment;their reaction to the nidotherapy intervention plan;their views on the acceptability and feasibility of individual- or community-level interventions when relevant;the areas of positive change in themselves or their community that they link to the intervention;areas of less positive changes that they associate with the intervention.

These prompts have been chosen from clinical experience and the results of previous studies of nidotherapy. Interviews will be recorded and transcribed, with audio and text stored securely in line with General Data Protection principles. Data will be coded using Lumivero NVivo (version 15 for Mac OS; Lumivero, Denver, Colorado, USA; https://lumivero.com/products/nvivo/). A minimum of five participants will be selected, after which point participants will continue to be recruited until thematic saturation is reached (we anticipate this to be between 7 and 12 people – see https://www.ncbi.nlm.nih.gov/pmc/articles/PMC7200005/). A summarising description of limited non-identifiable demographic details (age, gender, brief description of the participant’s intervention) will be included for those interviewed. This qualitative work will follow the consolidated criteria for reporting qualitative research (COREQ) guidelines.

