**Method:**

Adults in six villages will be offered a full personal environmental assessment followed by agreed change in different 3-month periods over the course of 1 year. All six villages have populations between 51 and 100 residents and are similar demographically. Assessments of mental health, personality status, social function, quality of life and environment satisfaction will be made. After the initial baseline period of 3 months, two villages will be randomised to nidotherapy for 3 months, a further two at 6 months and the last two at 9 months.

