## Method

The trial design is a cluster-randomised controlled trial using a step-wedge design of nidotherapy to be given to all adult residents (18 or over) in six villages in Nottinghamshire in central England. The plan is to randomise the six villages into three clusters each containing two villages, with active nidotherapy being given to each cluster for a period of 3 months. As the project will explain the principles of nidotherapy from the start of the study, when the people in villages are not receiving active nidotherapy, they will represent an unexposed passive nidotherapy control population.

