### Study setting

The six villages are Cotham, Hawton, Kilvington, Alverton, Thorpe and Staunton (total estimated eligible population, 300). Each village has similar population demographic characteristics with most residents over the age of 60, with no economically deprived areas, with most people living in owned properties. Each village has a church but no shops or other amenities.

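### The acceptability interviews draw only on trial completers, so nobody who withdrew can be heard, and with 7 to 12 interviews at least one village will usually have no interviewee

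*Protocol article*

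**What the plan says.** Under Qualitative project, the protocol article gives as its first aim "Assess the acceptability and feasibility outcomes of nidotherapy". Selection is set in the same section: "A random non-stratified sample of trial completers will be approached, and those who consent will undergo semi-structured individual interviews". On numbers it says: "A minimum of five participants will be selected, after which point participants will continue to be recruited until thematic saturation is reached"; it adds that "we anticipate this to be between 7 and 12 people". The interview guide is to cover reactions to the plan, views on individual-level or community-level interventions where these apply, and both good and less good changes.

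Three other places bear on the rule:

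- **Nidotherapy villages.** The equipoise argument says residents might "view any attempts at intervention as interference in the smooth life of the village". The same section defines a community intervention as one needing at least 10 members of the village.
- **Ethical aspects.** Participants may withdraw whenever they wish and need give no particular reason.
- **Fourth assessment.** The adverse event scale and the scale for satisfaction with the interventions are described here, at the end of follow-up.

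On structure, the Method section states: "The plan is to randomise the six villages into three clusters each containing two villages".

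**The concern.** An acceptability study needs access to people who did not accept the intervention. Here the rule removes one such group altogether. Continuing to saturation does not repair this, because saturation is reached among the people who can be sampled and says nothing about those who cannot. The two end-of-trial scales do not clearly fill the gap either, since a participant who has left will not be there to complete them.

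The second feature is the lack of stratification. Nidotherapy is delivered village by village and a community intervention is tied to its village. A handful of people drawn at random from six villages may leave one or more of those experiences unreported.

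What is at stake is the acceptability and feasibility conclusion, which could read more favourably and more generally than the interviews allow.

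**Working it through.** **The plan's own figure.** The 7 to 12 interviews are an expectation about saturation taken from a cited source. No calculation is given, so there is none to reproduce.

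**Inputs from the protocol article.** Six villages in three steps of two (Method); interviews: minimum 5, 7 to 12 expected (Qualitative project); "total estimated eligible population, 300" (Study setting), against an adult population of 400 in the abstract; villages of 51 to 100 residents (abstract).

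**Assumptions.** Completers per village are not given, so they are varied. The withdrawal rate is not given, so it is varied too. Everyone approached is taken to be equally likely to consent.

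**Step 1. Withdrawers.** With completers only, the chance of interviewing a withdrawer is 0 at any sample size. If withdrawers were in the frame, a random sample of n would include at least one with probability 1 − (1 − d)^n, where d is the withdrawal rate:

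| d (assumed) | n = 7 | n = 12 |
|---|---|---|
| 5% | 30% | 46% |
| 10% | 52% | 72% |
| 20% | 79% | 93% |

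**Step 2. Village coverage, equal villages, large-population approximation.** By inclusion-exclusion, P(all six represented) = Σ (−1)^k C(6,k) ((6 − k)/6)^n, for k = 0 to 6.

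- n = 5: 0, since five people cannot cover six villages.
- n = 7: 720 × 21 / 6^7 = 15,120 / 279,936 = 0.054, so at least one village is missed with probability 0.946.
- n = 12: 1 − 0.673 + 0.116 − 0.005 = 0.438, so at least one is missed with probability 0.562.

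**Step 3. The same without replacement, 300 completers, 50 per village.** P(all six) = Σ (−1)^k C(6,k) C(300 − 50k, n) / C(300, n). The expected number of villages missed is 6 × C(250, n) / C(300, n).

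| n | At least one village missed | Expected villages missed | Both villages of a step missed |
|---|---|---|---|
| 5 | 100% | 2.40 | 38% |
| 7 | 94% | 1.65 | 17% |
| 8 | 88% | 1.37 | 11% |
| 9 | 80% | 1.13 | 7% |
| 10 | 72% | 0.94 | 5% |
| 11 | 63% | 0.78 | 3% |
| 12 | 54% | 0.64 | 2% |

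**Step 4. Sensitivity: at least one village missed, n = 7 and n = 12.**

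| Completers | n = 7 | n = 12 |
|---|---|---|
| 400, near-equal villages | 94% | 55% |
| 150, equal | 94% | 53% |
| 90, equal | 94% | 50% |
| 60, equal | 93% | 46% |
| Villages graded from 51 to 100 | 95% | 60% |
| Three of 51, three of 100 | 96% | 66% |

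The choice between 300 and 400 hardly matters. Unequal villages make coverage worse.

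**Step 5. After stratification.** One interview per village uses 6 and two per village use 12. Either way the chance of an unrepresented village is 0.

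**The case against.** The strongest reply is that the frame is people who completed the trial, not people who took up or liked nidotherapy. A resident who disliked the plan, or did not act on it, but completed the assessments can still be drawn, and the guide asks for less positive views. So a reader might infer that the rule shuts out everyone who found nidotherapy unacceptable. The documents do not support that: only those who withdrew are shut out. The remark about interference is made about residents in general, as an equipoise argument. It is not a forecast of withdrawal. Some objectors will never enrol, and interviewing withdrawers would not reach them.

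On villages, coverage of each one is not a stated aim, the villages are described as "All six villages have populations between 51 and 100 residents and are similar demographically", and not every village need have a community intervention. Five is a floor, so only at that floor is full coverage impossible. A reader might also infer that several villages, or a whole randomised step, will usually go unheard. The figures do not support this across the expected range: the expected number missed falls from 1.65 to 0.64, and the chance of losing a step from about 17% to about 2%. Random selection also has a merit, because it stops investigators choosing whom to hear.

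All of this stands, and it limits the point. It does not give withdrawers any route into the interviews, and random selection can be kept while both gaps are closed.

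**Conclusion.** The point holds in limited form. The completer-only rule gives withdrawers no chance of interview in a study whose purpose includes acceptability, so the conclusion is likely to lean favourable. The direction rests on the judgement that people who leave hold, on average, less favourable views. The amount cannot be sized without a withdrawal rate, and the article does not define a completer.

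Separately, at least one village will more often than not have no interviewee: about 94-95% at 7 interviews and 54-56% at 12, assuming equal villages. The risk reaches one half or just below only at 12 interviews with very few completers (50% with 90, 46% with 60). This matters to the extent that views on village-specific community interventions are wanted.

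The interviews are a side study and the primary outcome analysis is untouched. This is a cheap improvement, not a flaw in the trial's main comparison.

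**What to change.** Reword the selection rule under Qualitative project in three respects:

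1. Define the frame as all enrolled participants, including those who withdrew and agree to be contacted.
2. Select at random within village, with at least one interviewee per village. This takes six interviews and so fits inside the anticipated 7 to 12.
3. Report withdrawers' views descriptively, with no formal comparison against completers, since one or two interviews could not support one. If no withdrawer agrees, state that the acceptability findings are completers' views only.

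Random selection is kept, and so is saturation as the stopping rule once every village is represented. The cost is a few lines of wording and asking for permission to make contact. Some withdrawn participants will refuse, and one or two more interviews may be needed, especially if withdrawals are few and the random draw happens to include none. Residents who never joined remain out of reach, and the report should say so.

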### Ethical aspects

The study has been approved by the Schools of Business, Law and Social Sciences Research Ethics Committee (BLSS REC) (project number 1900275) at Nottingham Trent University. All those taking part in the study will receive a participation information sheet and complete a signed consent form. We will follow the Helsinki Declaration criteria in that participants will have the right to cease involvement in the study and to withdraw from the trial at any time and for any reason, without prejudice to any future care. An investigator may also withdraw a participant from the trial at any time in the interests of the participant’s health and well-being or for administrative reasons.

To improve participation in the trial there will be open meetings at centres in each of the villages and invitation for all to take part in the merits of agreed environmental change.

### Assessments

#### Baseline

All participants will receive a baseline assessment to determine eligibility and agreement to take part in all parts of the trial. This will be preceded by publicity from local news outlets.

Each of the participants agreeing to take part will complete the following assessments, deliberately chosen to be relatively short and easy to complete in all groups:the Short Social Functioning Questionnaire (SSFQ),^
25
^ a short version of a well-tested measure;^
26
^
the Structured Assessment of Personality – Abbreviated Scale (SAPAS);^
27
^
the Assessment of Personality Strengths Scale (APSS);^
28
^
the Hospital Anxiety and Depression Scale (HADS);^
29
^
the Personality Assessment Questionnaire for ICD-11 – Revised (PAQ-11-R);^
30
^
the Recovering Quality of Life (ReQoL) (10-item version);^
31
^
the Personality Assessment Schedule for ICD-11 (PDS-ICD-11);^
32
^
the PROMIS-Short Form for Social Isolation (PROMIS-SF) (a four-item scale for social cohesion) at initial and last assessment;^
33
^
a satisfaction scale and the SSFQ^
25
^ will be completed at the last assessment.

These data will be help to create a combined assessment of personality, with the Structured Personality Assessment from Notes and Documents (SPAN-DOC)^
34
^ tool.

These assessments will be made at interview and or by self-completed paper records immediately stored at a data protected facility to ensure confidentiality. These data will represent a mental health profile of each resident at each stage of the study.

Details of all nidotherapy actions will be recorded to establish the total costs of interventions.

After 3 months of initial data collection a short check will be made on any material changes since early recruitment. Two of the villages will then be randomised to nidotherapy independently by [name] (Fig. 1).

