### Statistical design

The trial will use a randomised clustered step-wedge design with two arms. In the first 3-month period, the residents in all villages will be assessed to evaluate their clinical status and their environmental wishes. After 3 months a short check will be made on any material changes since recruitment. Two randomisations will then be carried out in three steps over 1 year. After the first 3 months of baseline assessment, two of the villages will be independently randomised to receive nidotherapy, with the other four acting as unexposed controls. At 6 months, another two villages from the remaining four will be randomised to nidotherapy with the last two unexposed villages as controls; at 9 months these remaining two villages will receive nidotherapy. Thus, the two villages receiving nidotherapy at first randomisation will have three 3-month periods to observe the post-treatment effects, the second two will have two periods to observe the post-treatment effects and the last two villages will have nidotherapy completed 12 months after the trial starts, and a final follow-up will take place for all participants within the following 3 months, and at 6 and 9 months environmental and short clinical assessments will be repeated on all participants.

The analysis will be carried out using intention-to-treat together with imputation of missing data. Analysis will be separated into three components: (a) change in scores of the primary outcome (social function); (b) change in scores of all secondary outcomes, including costs; and (c) changes in environmental satisfaction. Comparison in mean changes of outcomes between the two groups will be conducted using random effects models or multilevel models under a generalised linear modelling framework. Multilevel models^
23
^ will take into account both cluster effects of villages and difference among individuals, while estimating intervention effects over time. Considering that participants are not being randomised into treatment groups, refined models to assess intervention effects could adjust for baseline measures and other possible confounders.

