### Second assessment: three months after nidotherapy input to the first two villages

The SSFQ, PROMIS and ReQoL assessments will be completed for all participants.

*Third assessment: 6 months after completion of baseline assessment and after nidotherapy input to the second two villages*

The SSFQ, PROMIS and ReQoL assessments will be completed for all participants.

*Fourth assessment: 9 months after completion of baseline assessment and after nidotherapy input to the last two villages.*

All the assessments at baseline will be repeated, together with satisfaction scales, including an adverse event scale derived from the work of Klatte et al^
35
^ to determine the nature of adverse events in either arm of the trial. Satisfaction with the village environment will be recorded as a general statement at all assessments and satisfaction with the interventions also assessed using an agreed scale.^
36
^

A record of the most positive and negative environmental events^
37
^ will be made at the termination of the trial and linked to the cost-effectiveness analysis.

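### PROMIS social isolation is scheduled at two assessments in one place and four in another; the two-assessment version leaves that scale without a concurrent control

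*Protocol article*

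**What the plan says.** **PROMIS.** In the protocol article, the Baseline list under Assessments includes the PROMIS short form for social isolation, with its own timing: "a four-item scale for social cohesion) at initial and last assessment". The visit-by-visit schedule then says, for the second assessment and again for the third, "The SSFQ, PROMIS and ReQoL assessments will be completed for all participants". For the fourth it says "All the assessments at baseline will be repeated, together with satisfaction scales", which brings PROMIS in again. Only one PROMIS instrument is named.

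**Final visit.** Statistical design says that "the last two villages will have nidotherapy completed 12 months after the trial starts" and that "a final follow-up will take place for all participants within the following 3 months". It says of the first pair of villages that they "will have three 3-month periods to observe the post-treatment effects", and it gives the second pair two such periods. It states no number for the last pair. The last visit in the schedule is headed "Fourth assessment: 9 months after completion of baseline assessment and after nidotherapy input to the last two villages".

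**The concern.** The two PROMIS instructions cannot both be followed: the scale is collected either on two occasions or on four. The choice matters because of the stepped-wedge design. Controls exist only while roll-out is under way, so a scale measured just at the start and the end misses every point at which treated and untreated villages can be compared. No later analysis can recover data that were not collected.

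Social isolation is not incidental to this trial. The introduction uses loneliness among older people living alone as its example of what community nidotherapy might improve, and the Interventions section mentions social isolation among the targets of community change.

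The final visit raises a smaller question: whether the follow-up after treatment described in Statistical design is the follow-up that the visit schedule delivers.

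**Working it through.** **Inputs.** Baseline occupies months 0 to 3. Pairs of villages start nidotherapy at months 3, 6 and 9 (Abstract, Statistical design), and each block lasts 3 months. The interim visits are at months 6 and 9: Statistical design has "at 6 and 9 months environmental and short clinical assessments will be repeated on all participants", and the third assessment, 6 months after baseline completion, is 3 + 6 = month 9. The fourth assessment is 3 + 9 = month 12. A village counts as exposed at a visit once its block has begun before that visit.

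**Step 1: exposed and unexposed villages at each visit.**

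| Visit | Month | Exposed | Unexposed | PROMIS per Baseline list | PROMIS per visit schedule |
|---|---|---|---|---|---|
| Baseline | 3 | 0 | 6 | yes | yes |
| Second | 6 | 2 | 4 | no | yes |
| Third | 9 | 4 | 2 | no | yes |
| Fourth | 12 | 6 | 0 | yes | yes |

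Visits with both kinds of village present: none on the Baseline list, two on the visit schedule.

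**Step 2: can the effect be estimated?** Take a model with a treatment indicator and one effect per period.

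- Two occasions: three columns (treatment, first period, last period). Treatment is 0 for all villages at the first and 1 for all at the last, so its column equals the last-period column. The rank is 2 of 3, and treatment is fully aliased with time. Moving the last visit to month 15 changes nothing, because all six villages are still exposed.
- Four occasions: five columns, rank 5 of 5. The effect is estimable.

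The rank result depends on no assumed variance. For illustration only, a village-mean model with a random village intercept, assumed intracluster correlation 0.01 to 0.10 and 50 to 67 residents per village (300/6 to 400/6, the article's two population figures, assuming full participation) gives a standard error of about 0.09 to 0.10 SD on four occasions. On two occasions there is no estimate.

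**Step 3: post-treatment periods.** Periods = (month of final visit − month the block ends) / 3, with blocks ending at months 6, 9 and 12.

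- Final visit at month 15: (15 − 6)/3 = 3, (15 − 9)/3 = 2, (15 − 12)/3 = 1. This reproduces the stated three and two.
- Final visit at month 12: (12 − 6)/3 = 2, (12 − 9)/3 = 1, (12 − 12)/3 = 0.
- Final visit at month 12, counting from the start of treatment: (12 − 3)/3 = 3, (12 − 6)/3 = 2, (12 − 9)/3 = 1. This also yields three and two, but only by counting the treatment block as post-treatment.

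**The case against.** **The visit schedule probably shows the intention.** It names PROMIS at both interim visits and for everyone. The Baseline clause does not say that PROMIS is taken only at those two times. The next entry in that list mentions the SSFQ at the last assessment, although the SSFQ is taken at every visit, so timing remarks there are not exhaustive. Fig. 1, the project timeline, is not available here and may show the intended version. This makes leftover wording the likeliest explanation. It does not remove the conflict, because staff working from the Baseline list would omit the scale at the visits that matter.

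**The scale is a supporting measure.** Social isolation is not named among the secondary outcomes in the abstract or in the objectives. That stands, and it limits the weight of the point.

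**The timing texts overlap.** Month 12 is the opening edge of the window from month 12 to month 15, so a visit at or just after month 12 satisfies both. That stands too. What remains is the period count, which fits month 12 only on a loose reading of post-treatment. That reading is not impossible, since the Interventions section expects the main components to be finished within 2 months.

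**Stronger readings that a reader might infer.**

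- That the trial loses its controlled comparisons. It does not: the SSFQ and ReQoL are listed at all four assessments.
- That a 3-month final window lets villages be assessed in different seasons. The window is stated for all participants, and nothing says that villages would be seen at systematically different times within it. The exposed-versus-unexposed contrasts at months 6 and 9 do not rest on that visit.
- That follow-up is overstated for every pair. A count is given for two pairs only.

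**Conclusion.** The PROMIS schedule is internally contradictory. If the Baseline list is followed, the effect of nidotherapy on social isolation cannot be separated from time: no visit out of two has a concurrent control, against two visits out of four on the visit schedule. At the final visit the pairs would still differ in time since treatment, but that comparison has no untreated village in it. The conclusion rests on the stated roll-out and on allowing for period effects, not on any assumed correlation or village size.

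Among the three scales listed for the interim visits, only PROMIS is in doubt. HADS and the personality scales are listed only at baseline and the fourth assessment. The article is consistent about that, so it is not part of this contradiction.

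The final-visit timing is a secondary matter of clarity. The stated three and two periods match month 15; month 12 gives two and one unless the treatment block is counted. Because the texts overlap at month 12, this is a mismatch to tidy and not a demonstrated flaw in the comparison.

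**What to change.** In the Baseline list, delete the clause that ties PROMIS to the first and last assessments, so that the scale is taken at all four as in the visit schedule. Check that Fig. 1 agrees. The cost is one wording change and four items at two visits already planned, where the SSFQ and ReQoL are being collected anyway.

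Separately, state one time for the final assessment in both Statistical design and the fourth-assessment heading, and make the period count match. For a visit at month 12 the counts after treatment are two and one for the first two pairs, with none for the last. For a visit at month 15 they are three and two, with one for the last. This costs wording only.
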